## **2 Objectives**

### **2.1 Primary Objectives**

The primary study objective is to determine the risks of 12 months of DAPT vs a 6-month of DAPT followed by 6 months of aspirin monotherapy or clopidogrel monotherapy on gastrointestinal mucosal injury after DES implantation.

### **2.2 Secondary Objectives**

The secondary objective is to evaluate the feasibility and safety of AMCE as a method for detecting gastrointestinal mucosal injury and bleeding in patients receiving APT.

### **2.3 Exploratory Objectives**

The exploratory objective is to establish a gastrointestinal mucosal injury scoring system that may identify patients at future risk for clinical gastrointestinal bleeding during long-term APT.

For this purpose, 2 previously developed scoring systems will be used to assess the degree of mucosal injury observed by AMCE: (1) The modified Lanza score (MLS), and (2) a separate 5-point scoring system (See in protocol Appendix 2).

## **3 Study Design**

### **3.1 Overall study design and flow chart**

The OPT-PEACE is a multicenter, randomized, double-blind, placebo-controlled trial to evaluate the efficacy and safety of antiplatelet monotherapy with aspirin or clopidogrel between 6 and 12 months after DES implantation following 6 months of

DAPT detected by AMCE. All enrolled patients with a negative screening AMCE examination will be treated with open-label aspirin (100 mg/d) plus clopidogrel (75 mg/d) for 6 months. After 6 months, patients free from interval major adverse ischemic or clinically overt bleeding events and otherwise without any exclusion criteria (**section 3.2**) will undergo a second AMCE examination before randomization. Patients successfully completing this exam are then randomly assigned in a 1:1:1 ratio to receive aspirin plus clopidogrel, aspirin plus clopidogrel-placebo or clopidogrel plus aspirin-placebo for an additional 6 months in a double blinded manner.

[figure not shown]

**Figure 1. Study flowchart of the OPT-PEACE trial**

### 3.2 Inclusion/Exclusion criteria

Patients with either stable coronary artery disease or low-risk acute coronary syndromes without ST-segment elevation (GRACE score<140) after complete coronary revascularization with at least 1 but not more than 4 contemporary DES will be eligible for the OPT-PEACE study.

Enrollment into the study will require meeting all inclusion AND none of the exclusion criteria. Patients meeting all entry criteria will provide informed written consent and then undergo a screening AMCE examination 30–120 hours after successful PCI. Only those without ulceration or bleeding by AMCE will be enrolled.

Inclusion criteria are listed below.

- (1) Adult patients with age 18–80 years;
- (2) Presentation with silent ischemia, stable angina, or non-ST-segment elevation acute coronary syndrome with GRACE score<140 at admission;
- (3) PCI with implantation of contemporary DES(s) during the present admission.

*The contemporary DES refers to DES with thin cobalt-chromium or platinum-chromium struts, with a durable or biodegradable polymer eluting a rapamycin-analogue anti-proliferative agent. The current major DES available in China market include: EXCEL and EXCEL 2 (JW Medical System, Weihai, China), Tivoli(Essen Technology, Beijing, China), Endeavor Resolute (Medtronic Inc, Minnesota, USA), FireHawk (MicroPort Medical (Group) Co, Ltd, Shanghai, China), BuMA (SinoMedical, China), Xience V (Abbott, Abbott Park, Illinois, USA), Xience Prime (Abbott Laboratories, Abbott Park, Illinois, USA), Promus Element and Synergy (Boston Scientific, Massachusetts, USA)].*

- (4) Complete revascularization (successful PCI treatment of all epicardial coronary lesions with diameter stenosis <70% or intermediate lesions with FFR $\leq$ 0.80);
- (5) Planned DAPT with aspirin and clopidogrel for at least 6 months;
- (6) Agreement to comply with all study procedures;
- (7) Written informed consent provided.

Meanwhile, patients should not enter the study if any of the following exclusion criteria are met:

- (1) Presentation with STEMI;
- (2) Left main disease (diameter stenosis>30%);
- (3) Any prior coronary stent implantation during the last year prior to the index procedure;
- (4) Implantation of first-generation drug-eluting stents or bioabsorbable scaffolds during the index procedure;
- (5) Implantation of >4 stents during the index procedure;
- (6) Any prior stent thrombosis;
- (7) Any active gastrointestinal bleeding or ulcers, or prior gastrointestinal bleeding or ulcers within the last 24 months;
- (8) Prior gastrointestinal tract or abdominal surgery other than simple procedures which would not change the gastrointestinal tract anatomy, such as polyp removal, cholecystectomy or appendectomy;
- (9) Contraindications to the AMCE test, including suspected or known gastrointestinal obstruction, stenosis, fistula, diverticula, etc; presence of gastrointestinal obstruction symptoms such as pain or dysphagia; inoperative conditions or refusal to undergo abdominal surgery if required (ie, if the capsule will not pass and cannot be removed by endoscopy);
- (10) Severe hemorrhoids (phase 3–4 according to guidelines of American Society of Colon and Rectal Surgery);
- (11) LVEF<0.40 on admission by echocardiography;
- (12) Renal dysfunction (eGFR<30 ml/min/1.73m^2);
- (13) Active hepatitis or ALT >3 times upper limits of normal at admission;

- (14) Uncontrolled severe hypertension (>180/110 mmHg);
- (15) Hemoglobin<100 g/L;
- (16) Platelet count<100 × 10^9/L;
- (17) Planned use of a proton pump inhibitor, gastric mucosa protectant or any other antacid agent after study enrollment;
- (18) Required use of oral anticoagulation (warfarin or other factor II or factor X inhibitors);
- (19) Inability to take 12-month DAPT for any reason;
- (20) Mandatory use of >6-month DAPT;
- (21) Any comorbidity with estimated survival time<12 months (eg, progressive cancer, chronic obstructive lung disease, etc);
- (22) Any contraindication to MRI examination, including implantation of an MRI-incompatible pacemaker, defibrillator, or other ferromagnetic material, etc;
- (23) Pregnant or plan to be pregnant within 1 year;
- (24) Any condition that may interfere with any study procedures, such as dementia, immobility, alcohol use, etc;
- (25) Planned surgery within 1 year;
- (26) Taking iron supplement;
- (27) Participating in any other clinical trial of an investigational drug or device that has not met its primary endpoint.

### **3.3 Subject randomization**

The eligibility for randomization for all enrolled patients will be evaluated at 6 months (±2 weeks), including medication adherence and the interval occurrence of adverse events. The patients with any of the following will not be randomized:

- (1) Withdrawal of informed consent;
- (2) Lost to follow-up at 6 months;
- (3) Any event in the prior 6 months which in the opinion of the investigator results in the patient not being suitable for randomization of antiplatelet agent regimen either because of a) necessity to continue dual antiplatelet therapy (eg, major adverse cardiovascular or cerebrovascular event within the prior 6 months or need for repeat stenting), or b) inability to continue dual antiplatelet therapy (eg, bleeding, neoplasm, need for urgent surgery, etc within the prior 6 months);
- (4) Not presently taking both aspirin and clopidogrel, or any prior temporary discontinuation of aspirin or clopidogrel for  $\geq 5$  days;
- 5) Use of proton pump inhibitors or gastric mucosal protectants for more than 12 days, or for more than 4 continuous days in the 6 months prior to randomization\*;
- (6) Unwillingness or inability to undergo the 6-month AMCE examination or the remainder of the study procedures, including the 12-month AMCE exam.

At this time patients free from interval major adverse ischemic or clinically overt bleeding events and otherwise without any above-mentioned exclusion criteria will undergo a second AMCE examination before randomization. Patients successfully completing 6-month follow-up AMCE exam and with no ulceration or bleeding are then randomly assigned in a 1:1:1 ratio to receive aspirin plus clopidogrel, aspirin plus clopidogrel-placebo or clopidogrel plus aspirin-placebo for an additional 6 months in a double blinded manner.

Randomization is stratified according to site and will be performed in fixed block of sizes 6 and block sizes will not be revealed to sites. The electronic data capture system (EDC) will be used to randomize subjects. The EDC will assign a treatment arm for patients and specify the appropriate medication number for the package of investigational treatment to be dispensed to the patient.

Enrolled patients who do not meet eligibility for randomization will not receive any more study drugs, and subsequent antiplatelet therapy will be administered at their attending physicians' discretion in accordance with the local standard of care. All

enrolled patients, irrespective of eligibility for randomization, should be followed up until 12 months.

### **3.4 Blinding and procedures for unblinding the study**

#### **3.4.1 Methods for ensuring blinding**

This study has a double-blind design with aspirin, clopidogrel, and matching placebos. The active tablets and the respective placebo tablets will be identical in size, color, smell, and taste. The patients, site personnel, sponsor personnel, persons performing the assessments, and data analysts will remain blinded to the identity of the treatment from the time of randomization until completing the statistical analysis. There will be an independent data safety monitoring board (DSMB) to monitor the data on a periodic basis.

All AMCE images will be assessed by a core laboratory (Digestive Endoscopy Center, Department of Gastroenterology, Shanghai Changhai Hospital, Second Military Medical University, Shanghai, China) blinded to patient allocations.

#### **3.4.2 Methods for unblinding patients' treatment assignment**

In emergency situations, in which knowledge of the investigational drug is critical to the subject's medical management, the blind for that subject may be broken by the treating physician to provide optimal management. Before breaking the blinding, the consent of the research leader of the participating research site should be obtained and the relevant researchers and monitors should be informed. At the same time, the events leading to break the blinding and the blind code information should be recorded in detail. After breaking the blinding, the subject will not receive any study drug, and the treated physician can take corresponding bail-out measures according to local standard of care. The study drugs cannot be resumed even if the condition of subject is stable, while researchers still need to conduct clinical follow-up for 12 months for the subject with broken blinding, and AMCE examination is still required. Researchers should withdraw the study drugs from the patients whose blinding was broken.

## 3.5 Treatments

### 3.5.1 Identity of Investigational Product

The investigational product is enteric coated aspirin 100 mg tablets and matching aspirin-placebo tablets, and clopidogrel 75 mg and matching clopidogrel-placebo tablets.

**Table 1 Identity of Investigational Product**

| Study drug           | The form and dosage of drug | Manufacturer                                      |
|----------------------|-----------------------------|---------------------------------------------------|
| Bayaspirin (aspirin) | 100mg tablet                | Bayer                                             |
| Aspirin-placebo      | tablet                      | Guangzhou Boji Medical Biotechnological co., Ltd. |
| Plavix (clopidogrel) | 75mg tablet                 | Sanofi-Aventis                                    |
| Clopidogrel-placebo  | tablet                      | Guangzhou Boji Medical Biotechnological co., Ltd. |

### 3.5.2 Doses and treatment regimens

After enrollment, patients will routinely administer study drugs (including open-label aspirin at a dose of 100mg swallowed with 100ml warm water 30 minutes daily before breakfast, plus open-label clopidogrel at a dose of 75mg daily) until the face-to-face study visit at 6 months. At the face-to-face study visit, randomized participants will be allocated study drugs (including: Group A, blinded-label aspirin at a dose of 100mg daily, plus blinded-label clopidogrel at dose of 75mg daily; Group B, blinded-label aspirin at a dose of 100mg daily, blinded-label clopidogrel-placebo at dose of 75mg daily; Group C, blinded-label aspirin-placebo at a dose of 100mg daily, plus blinded-label clopidogrel at dose of 75mg daily) and should be used regularly until the end of study.

### 3.6 Study variables

Data collection commences after the subject has provided informed consent. Data collection including subject demographic information, laboratory tests, and procedural data, AMCE examination data, as well as follow-up visits or telephone contacts will be conducted by an Investigator or site coordinator who has been trained on the protocol and Case Report Forms (CRF). Data required for analysis will be obtained as outlined in Table 2.

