### **6.2.3 Face-to face follow-up procedure at 12 months (for randomized subjects)**

- Assess for adverse events may include, but not be limited to MI, stroke, revascularization, bleeding and ST
- Conduct the third AMCE examination to observe gastrointestinal mucosal lesions
- Review concomitant medications with subject
- Recycle and count all of remaining study drugs

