### **7.3.4 Adverse Events based on signs and symptoms**

When collecting AEs, the recording of diagnoses (when possible) is preferred to

recording a list of signs and symptoms. However, if a diagnosis is known and there are other signs or symptoms that are not generally part of the diagnosis, the diagnosis and each sign or symptom will be recorded separately.

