## **11.2 Secondary Endpoint**

1. The incidence and severity of gastric and intestinal mucosal lesions during the first 6 months after study enrollment (prior to randomization);
2. The incidence and severity of gastric and intestinal mucosal lesions after randomization (i.e., between 6 months and 12 months after study enrollment);
3. The incidence of clinically evident gastrointestinal hemorrhage attributed to the upper GI tract (or of unknown origin) during 6 months after study enrollment (prior to randomization);
4. The incidence of clinically evident gastrointestinal hemorrhage attributed to the upper GI tract (or of unknown origin) after randomization (i.e., between 6 months and 12 months after study enrollment);
5. The incidence of clinically evident gastrointestinal hemorrhage attributed to the upper GI tract (or of unknown origin) during 12 months after study enrollment;
6. Gastrointestinal symptoms (pain, nausea/vomiting, dysphagia, other) during the 12 months after enrollment;
7. All bleeding (BARC types 1–5) during the 12 months after enrollment;
8. The incidence of target lesion failure (TLF; cardiac death, target-vessel MI, or clinically-driven target lesion revascularization), during the 12 months after enrollment;
9. The incidence of net adverse clinical events (NACE, defined as TLF or BARC type 2–5 bleeding) during the 12 months after enrollment;
10. The incidence of stent thrombosis (ARC definite, probable, or definite/probable) during the 12 months after enrollment.

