## 17. APPENDIX 3 – GASTROINTESTINAL SYMPTOM

### SCORE

Symptoms are categorized as four types: abdominal pain, bloating, acid reflux, and belching.

Each symptom includes a five-level scoring system (degree and frequency are scored separately; the maximum score = 4 + 4 = 8 points).

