### 4.2 Secondary variables

Secondary endpoints listed below will be evaluated.

1. The incidence and severity of gastric and intestinal mucosal lesions (a composite of erosion, ulceration or bleeding) during the first 6 months after study enrollment (prior to randomization);

2. The incidence and severity of gastric and intestinal mucosal lesions (a composite of erosion, ulceration or bleeding) within 6 months after randomization (between 6 months and 12 months after study enrollment);

3. The incidence of clinically evident gastrointestinal hemorrhage attributed to the upper GI tract (or of unknown origin) during 6 months after study enrollment (prior to randomization);

4. The incidence of clinically evident gastrointestinal hemorrhage attributed to the upper GI tract (or of unknown origin) after randomization (ie, between 6 months and 12 months after study enrollment);

5. The incidence of clinically evident gastrointestinal hemorrhage attributed to the upper GI tract (or of unknown origin) during 12 months after study enrollment;

6. Gastrointestinal symptoms within 6 months after enrollment, within 6 months after randomization, and within 12 months after enrollment (details in Protocol Appendix 3);

7. All bleeding (BARC types 1–5) events within 6 months after enrollment, within 6 months after randomization, and within 12 months after enrollment;

8. The incidence of target lesion failure (TLF; cardiac death, target-vessel MI, or clinically-driven target lesion revascularization), during the 12 months after enrollment;

9. The incidence of net adverse clinical events (NACE, defined as TLF or BARC type 2–5 bleeding) within 6 months after enrollment, within 6 months after randomization, and within 12 months after enrollment;

10. The incidence of stent thrombosis (Academic Research Consortium defined definite/probable) within 6 months after enrollment, within 6 months after randomization, and within 12 months after enrollment.

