##### 2.1.11.1 Ordinal frequency of gastrointestinal symptoms assessment at baseline

##### 2.1.11.2 Ordinal frequency of gastrointestinal symptoms assessment at 6 months

##### 2.1.11.3 Ordinal frequency of gastrointestinal symptoms assessment at 12 months

### 2.2.1 Site reported AEs/SAEs

2.2.1.1 12 months binary frequency and KM estimates of TLF

2.2.1.2 12 months binary frequency and KM estimates of all bleeding

2.2.1.3 12 months binary frequency and KM estimates of NACE

2.2.1.4 12 months binary frequency and KM estimates of stent thrombosis

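### The Appendix 3 GI symptom score is scheduled at no visit, so the planned ordinal analysis and ordinal tables of secondary endpoint 6 are not secured

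*Supplement*

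**What the plan says.** **The endpoint.** SAP 4.2, item 6, reads "Gastrointestinal symptoms within 6 months after enrollment, within 6 months after randomization, and within 12 months after enrollment (details in Protocol Appendix 3". Protocol 11.2, item 6, reads "Gastrointestinal symptoms (pain, nausea/vomiting, dysphagia, other) during the 12 months after enrollment".

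**The instrument.** Protocol Appendix 3 states "Symptoms are categorized as four types: abdominal pain, bloating, acid reflux, and belching". Each symptom is graded on five levels: "degree and frequency are scored separately; the maximum score = 4 + 4 = 8 points". Frequency is graded in episodes per week. The appendix names no visit and no recall period.

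**The analysis.** SAP 9.3.1 lists GI symptoms as the only ordinal variable, cites Appendix 3, and compares groups by proportional odds logistic regression. SAP 11 lists ordinal symptom tables at baseline and 6 months for the enrolled cohort, and at baseline, 6 and 12 months for the randomised cohort. The last of these is "Ordinal frequency of gastrointestinal symptoms assessment at 12 months".

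**The data collection.** SAP 3.6 states "Data required for analysis will be obtained as outlined in Table 2", and Protocol 6.2 says the same. The 12-month visit list in Protocol 6.2.3 includes "Conduct the third AMCE examination to observe gastrointestinal mucosal lesions", an adverse event assessment, a medication review and a pill count. It does not include the symptom score.

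**The concern.** The plan uses a graded instrument as the outcome of a regression model, and it points to one table as the source of the analysis data. That table and the visit procedures omit the instrument. A site that follows the schedule exactly would not administer it. The grades would then be absent, or would have to be reconstructed afterwards from memory or notes.

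Three things are at stake: the treatment comparison on symptom severity, the ordinal tables, and a pre-randomisation score that could serve as a covariate. The score also has no set time relative to the capsule examination, which falls at the same three visits. Its preparation can itself leave patients feeling bloated.

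**Working it through.** No formula applies. The check sets what the analysis needs against what the latest documents (Protocol v1.4 and the SAP) schedule.

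**1. What the analysis needs.** A degree grade (0 to 4) and a weekly frequency grade (0 to 4), giving 4 + 4 = 8 at most per symptom, at baseline, 6 and 12 months.

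**2. Where the score should be scheduled.**

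| Place | Score named? |
|---|---|
| Protocol Table 2 | No |
| SAP Table 2 | No |
| Protocol 6.2.1 (enrolment) | No |
| Protocol 6.2.2 (6 months) | No |
| Protocol 6.2.3 (12 months) | No |

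That is 0 of 2 schedule tables and 0 of 3 visit lists. The tables are otherwise detailed. They have rows for height and weight, the HP breath test, faecal occult blood, and platelet testing in a subset of 102 patients (34 per group).

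**3. What is collected on GI symptoms.**

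- Protocol 6.3: symptoms such as distension, nausea and vomiting, taken as safety variables at follow-up contacts. They are ungraded, and the wording does not reach baseline.
- Protocol 7.3.1: all GI adverse events from consent to study exit. Both Tables 2 carry an adverse event row at visits 1, 2 and 3.
- Protocol 12.4: GI symptoms are on the events committee's list. The committee adjudicates reported events; it does not administer a score. The list refers to Appendix 1 for definitions, and Appendix 1 holds no symptom score.

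**4. Can the score be derived from those records?** No, for three reasons.

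- The items in Protocol 7.3.3 (description, dates, seriousness, causality, action, outcome and similar) include neither a 0 to 4 degree nor a weekly frequency.
- Protocol 7.1 defines an adverse event as a new condition or a worsening. Stable, pre-existing reflux or belching would earn Appendix 3 points but need never be reported, so the baseline distribution cannot be rebuilt.
- Protocol 7.3.4 prefers a diagnosis to a list of its symptoms. Separate recording applies only "However, if a diagnosis is known and there are other signs or symptoms that are not generally part of the diagnosis".

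**5. Do the symptom lists agree?**

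| Protocol 11.2 and SAP 9.3.1 | Appendix 3 |
|---|---|
| Pain | Abdominal pain |
| Nausea/vomiting | Not graded |
| Dysphagia | Not graded |
| Other | Bloating, acid reflux and belching have no named counterpart |

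Only pain is named in both. SAP 9.3.1 gives the left-hand list and cites the right-hand one for the same variable.

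**6. Extent.** One of ten secondary endpoints; 2 + 3 = 5 ordinal tables in SAP 11 (two enrolled-cohort, three randomised-cohort); 480 patients planned for randomisation.

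**The case against.** **Symptom data are collected.** A reader might infer from the schedule that endpoint 6 would have no data at all. The documents do not support that. Protocol 6.3, Protocol 7.3.1 and the adverse event rows yield symptom occurrence, and Protocol 7.3.4 would record symptoms that lack a diagnosis. An incidence summary over 12 months is feasible and would answer the endpoint as Protocol 11.2 words it. This part of the objection stands; what is unsecured is the graded score.

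**Table 2 is not exhaustive.** Creatinine is in Protocol 6.2.1 but has no row in Table 2. Procedural data are to be collected and tabulated, also without a row. SAP 11 names the symptom assessment times, and the case report form is not shown. So a missing row does not prove missing data. This also stands. However, creatinine and procedural data are each named somewhere in the collection text, and the symptom score is not.

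**Bowel preparation.** A reader might infer that a score taken around the capsule examination would measure the procedure rather than the drugs. That goes too far. Preparation is the same in all three blinded arms, and frequency is graded per week, so a single purge is unlikely to dominate. The effect is noise, not bias between arms. The concern is still reasonable for the degree grade: Protocol 5.6.3 has patients drink 500 to 1000 ml until full, bloating is an Appendix 3 item, and SAP 4.3 treats distension after the examination as an event of interest.

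**The covariate is optional.** The SAP's binary models contain treatment only, and a single 12-month score is not the same as an endpoint defined over three windows. It is true that adjustment is a refinement rather than a correction. But SAP 11 already plans to tabulate the 6-month score, and randomisation takes place at that visit. The other windows can be kept as descriptive summaries.

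**Conclusion.** The point holds as an omission from the schedule. Followed to the letter, the plan yields unscored symptom and adverse event data. From these the proportional odds analysis in SAP 9.3.1 and the five ordinal tables in SAP 11 cannot be produced. The gap is clearest at baseline, where neither the follow-up contacts in Protocol 6.3 nor the adverse event definition would capture existing symptoms.

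The reach is limited to one of ten secondary endpoints, and neither the primary analysis nor the sample size is affected. The conclusion assumes that sites work from Table 2 and the visit lists. If the case report form already carries the score, the data may exist and the fault is a mismatch between documents. The missing recall period and the conflicting symptom lists would need settling in either case.

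**What to change.** 1. Add a row *GI symptom score (Appendix 3)* at visits 1, 2 and 3 in both Tables 2, and a matching item in Protocol 6.2.1, 6.2.2 and 6.2.3. At visit 2 it should be completed before randomisation.
2. State the recall period, and require completion before bowel preparation to limit procedure-related noise.
3. Reconcile the symptom list in Protocol 11.2 and SAP 9.3.1 with the one in Appendix 3. In doing so, state how the four symptom scores enter the ordinal model, because Appendix 3 gives a maximum of 8 per symptom but no rule for combining them.
4. In SAP 9.3.1, make the post-randomisation comparison by proportional odds regression with the 6-month (pre-randomisation) score as a covariate. Keep the other windows in SAP 4.2 as descriptive summaries.

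The cost is a minor amendment to both documents and, if the case report form lacks the score, one short page that takes a few minutes per visit. If the page already exists, only the tables, the visit lists, the definitions and the model text change.
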